## 10. Sample Size Calculation

The research hypothesis is that the "salt substitute intervention would significantly reduce the systolic blood pressure of patients with hypertension", with the test power of 0.80 and the significance level at 0.05. According to previous studies, consuming salt substitutes for a prolonged period can lower the systolic blood pressure of patients with hypertension by roughly 2~5mmHg. This research hypothesizes that the systolic blood pressure of the elderly participants would decrease by 3.0mmHg, with a standard deviation of 18mmHg. Since the number of groups is 48 and the intra-group correlation coefficient is 0.02, 16 participants are needed in every group calculated by NCSS-PASS software. In addition, considering that about 20% of the participants might be lost to follow-up or be removed from the research due to non-compliance, it is finally determined that 20 participants will be included in each nursing home, for a total of 960 participants across 48 nursing homes.

Based on the sample size calculated above, the sample size for the four intervention groups is as follows:

|                   |     | SS intervention |     |       |
|-------------------|-----|-----------------|-----|-------|
|                   |     | Yes             | No  | Total |
| SSSC intervention | Yes | 240             | 240 | 480   |
|                   | No  | 240             | 240 | 480   |
| Total             |     | 480             | 480 | 960   |

For the other intervention strategy, it can be estimated from the previous research experience that the SSSC intervention strategy can reduce the systolic blood pressure of the elderly by 4.0mmHg. With the significance level, number of groups, and intra-group correlation coefficient constant, and based on the sample size calculated above, it can be concluded that the power of applying this intervention strategy to reducing systolic blood pressure by 4.0mmHg will be 96.6%.

Given the potential changes of actual systolic blood pressure difference during the trial and the number of participants recruited from each facility, the changes to the trial power will follow the trend below:

[figure not shown]

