## **2.5 Sample size**

The study was designed to provide at least 80% power (with a 2-sided  $\alpha = 0.05$ ) to detect a net reduction in mean SBP of at least 3.0 mm Hg between groups with either or both interventions compared to control. The power estimate assumed a standard deviation of systolic blood pressure of 18 mmHg based on previous studies, an intra-cluster correlation coefficient of 0.02, and a loss of follow-up rate of 20%, resulting in a sample size of 960 individuals drawn from 48 clusters, each with 20 participants.

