### **3.1 Confidence intervals and p values**

All applicable statistical tests will be 2-sided and will be performed using a 5% significance level. All confidence intervals presented will be 95% and two-sided.

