#### **5.1.1 Primary analysis**

The primary analysis will be performed in FAS dataset. The results will be regarded as the main findings.

A pre-specified linear mixed effects model will be performed to model repeated measures of SBP of the same individual over time. The model will include intervention status and baseline SBP as fixed effects, as well as cluster and time as random effects. Separated models will be built for each intervention, either SS alone or SSSC alone. The model would be:

$$y_{ijt} = \beta_0 + \mu_{1i} + \mu_{2j} + \beta_1 x_{ij} + \beta_2 c_{ij} + \beta_3 t + e_{ijt}$$

$$e_{ijt} \sim N(0, \sigma_e^2)$$

$$\mu_{1i} \sim N(0, \sigma_{\mu 1}^2)$$

$$\mu_{2j} \sim N(0, \sigma_{\mu 2}^2)$$

Where  $i$  represents the  $i^{\text{th}}$  subjects,  $j$  represents the  $j^{\text{th}}$  cluster (facility),  $t$  represents time point  $t$ ,  $y_{ijt}$  is the SBP measured for subject  $i$  in cluster  $j$  at time  $t$  (follow-up month), baseline SBP will not be included in  $y_{ijt}$ ;  $\beta_0$  is the mean outcome in the control group at baseline;  $\mu_{1i}$  is an individual random effect to allow for multiple repeats per person;  $\mu_{2j}$  is a cluster random effect on baseline SBP to allow for between-cluster heterogeneity;  $x_{ij}$ , the predictor of interest, either SS or SSSC, is an indicator of the intervention for subject  $i$  in cluster  $j$  (1 indicates receive intervention while 0 indicates not receive intervention);  $\beta_1$ , the coefficient of interest, is the effect coefficient of intervention;  $c_{ij}$  is the baseline SBP measured for subject  $i$  in cluster  $j$ ;  $e_{ijt}$  is the random error for the measurement of subject  $i$  in cluster  $j$  at time  $t$ .

The estimation of  $\beta_1$ , its 95% confidence interval and the corresponding  $p$  value will be reported in **Table 2**.

We will also evaluate the interaction between SS and SSSC in lowering SBP during study period. If the effect of both interventions do exist, we will add interaction term in the above model to test the interaction between SS and SSSC. The model would be:

$$y_{ijt} = \beta_0 + \mu_{1i} + \mu_{2j} + \beta_1 x_{1ij} + \beta_2 x_{2ij} + \beta_3 x_{1ij} * x_{2ij} + \beta_4 c_{ij} + \beta_5 t + e_{ijt}$$

$$e_{ijt} \sim N(0, \sigma_e^2)$$

$$\mu_{1i} \sim N(0, \sigma_{\mu 1}^2)$$

$$\mu_{2j} \sim N(0, \sigma_{\mu 2}^2)$$

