Where  $i$  represents the  $i^{\text{th}}$  subjects,  $j$  represents the  $j^{\text{th}}$  cluster (facility),  $t$  represents time point  $t$ ,  $y_{ijt}$  is the SBP measured for subject  $i$  in cluster  $j$  at time  $t$  (follow-up month), baseline SBP will not be included in  $y_{ijt}$ ;  $\beta_0$  is the mean outcome in the control group at baseline;  $\mu_{1i}$  is an individual random effect to allow for multiple repeats per person;  $\mu_{2j}$  is a cluster random effect

on baseline SBP to allow for between-cluster heterogeneity ;  $x_{1ij}$  , one of the predictors of interest, is an indicator of the intervention SS for subject  $i$  in cluster  $j$  (1 indicates receive SS while 0 indicates not receive SS);  $\beta_1$  , the coefficient of interest , is the effect coefficient of SS;  $x_{2ij}$  , one of the predictors of interest, is an indicator of the intervention SSSC for subject  $i$  in cluster  $j$  (1 indicates receive SSSC while 0 indicates not receive SSSC);  $\beta_2$  , the coefficient of interest , is the effect coefficient of SSSC;  $\beta_3$  is the effect coefficient of SS and SSSC interaction;  $c_{ij}$  is the baseline SBP measured for subject  $i$  in cluster  $j$ ;  $e_{ijt}$  is the random error for the measurement of subject  $i$  in cluster  $j$  at time  $t$ .

The estimation of  $\beta_1$  ,  $\beta_2$  ,  $\beta_3$  and their 95% confidence interval and the corresponding  $p$  value will be reported in **Table 2**.

We will not adjust for the multiple tests, i.e. we will test both primary aims at  $p=0.05$ , because the efficacy and effectiveness of salt substitute in lowering blood pressure has been proved in previous studies with RCT design and our current study on this specific intervention is considered an implementation study, which will inform us the effectiveness of applying the particular intervention in this particular setting, senior residential facilities. Only the SSSC is considered a novel intervention that has never been rigorously tested before.

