#### 5.1.2.1 Controlling for potential confounders

We will test if there is any imbalance between groups in baseline variables. We will additionally include the covariates that differs significantly at the baseline ( $p<0.05$ ) to adjust confounding.

The models would be:

$$y_{ijt} = \beta_0 + \mu_{1i} + \mu_{2j} + \beta_1 x_{ij} + \beta_2 c_{ij} + \sum BZ_{ij} + \beta_3 t + e_{ijt}$$

$$e_{ijt} \sim N(0, \sigma_e^2)$$

$$\mu_{1i} \sim N(0, \sigma_{\mu 1}^2)$$

$$\mu_{2j} \sim N(0, \sigma_{\mu 2}^2)$$

Where  $i$  represents the  $i^{\text{th}}$  subjects,  $j$  represents the  $j^{\text{th}}$  cluster (facility),  $t$  represents time point  $t$ ,  $y_{ijt}$  is the SBP measured for subject  $i$  in cluster  $j$  at time  $t$  (follow-up month), baseline SBP will not be included in  $y_{ijt}$ ;  $\beta_0$  is the mean outcome in the control group at baseline;  $\mu_{1i}$  is an individual random effect to allow for multiple repeats per person;  $\mu_{2j}$  is a cluster random effect on individual baseline SBP to allow for between-cluster heterogeneity;  $x_{ij}$ , the predictor of interest, either SS or SSSC, is an indicator of the intervention for subject  $i$  in cluster  $j$  (1 indicates receive intervention while 0 indicates not receive intervention);  $\beta_1$ , the coefficient of interest, is the effect coefficient of intervention;  $c_{ij}$  is the baseline SBP measured for subject  $i$  in cluster  $j$ ;  $Z_{ij}$  is the baseline covariate other than SBP measured for subject  $i$  in cluster  $j$ ;  $e_{ijt}$  is the random error for the measurement of subject  $i$  in cluster  $j$  at time  $t$ .

If the interaction effect in primary analysis exists, then below model will be built for adjustment of covariates:

$$y_{ijt} = \beta_0 + \mu_{1i} + \mu_{2j} + \beta_1 x_{1ij} + \beta_2 x_{2ij} + \beta_3 x_{1ij} * x_{2ij} + \beta_4 c_{ij} + \sum BZ_{ij} + \beta_5 t + e_{ijt}$$

$$e_{ijt} \sim N(0, \sigma_e^2)$$

$$\mu_{1i} \sim N(0, \sigma_{\mu 1}^2)$$

$$\mu_{2j} \sim N(0, \sigma_{\mu 2}^2)$$

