**Table 2. The effect of intervention on changes of primary outcome and secondary outcomes**

| SS                            |         | SSSC                          |         | p for interaction |
|-------------------------------|---------|-------------------------------|---------|-------------------|
| Difference of outcome (95%CI) | p value | Difference of outcome (95%CI) | p value |                   |
| Primary outcome        |         |                               |         |                   |
| SBP,mmHg                      |         |                               |         |                   |
| Secondary outcome      |         |                               |         |                   |
| DBP,mmHg                      |         |                               |         |                   |
| urinary sodium,mmol/d         |         |                               |         |                   |
| urinary potassium,mmol/d      |         |                               |         |                   |
| microalbumin, mg/d            |         |                               |         |                   |
| serum potassium,mmol/l        |         |                               |         |                   |
| serum sodium,mmol/l           |         |                               |         |                   |

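### In SAP 5.1.1 the interaction model's SS and SSSC coefficients are single-intervention v control contrasts, but they are labelled as the interventions' effects and sent to the same Table 2 columns as the main effects

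*Supplement*

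**What the plan says.** SAP 5.1.1 has two steps. First, a separate mixed model for each intervention with a single 0/1 indicator. Its β1 contrasts all facilities receiving that intervention with all that do not, over both levels of the other factor, and goes to Table 2 with its interval and p value. The SAP describes these models as SS alone or SSSC alone, which can only mean one indicator in the model, not the single-intervention arm.

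Second, if both interventions have an effect, "we will add interaction term in the above model to test the interaction between SS and SSSC". Both indicators stay 0/1. For β1 the SAP says "the coefficient of interest , is the effect coefficient of SS", and it uses the matching phrase for β2 and SSSC. β1, β2 and β3 all go to Table 2 with intervals and p values.

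The Table 2 shell, titled "The effect of intervention on changes of primary outcome and secondary outcomes", has one difference and one p value for SS, the same for SSSC, and one p value for interaction. Nothing says which model fills the SS and SSSC columns once both have been fitted. SAP 5.2.1 applies the same models to the continuous secondary outcomes.

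SAP 5.1.2.1 sets out the adjusted single-indicator models and then adds: "If the interaction effect in primary analysis exists, then below model will be built for adjustment of covariates". Results go to Table 3. SAP 5.3.2.1 gives a logistic interaction model for hyperkalemia with the same 0/1 form.

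**The concern.** Once a product of 0/1 indicators is in the model, the coefficient of one indicator is that intervention's effect where the other is absent. It is no longer the effect averaged over the other factor. The SAP keeps the general label and the same destination, so a reader of Table 2 could not tell which quantity was printed.

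Two consequences follow. Without interaction, the interaction-model coefficients estimate the same number less precisely, and could look inconsistent with main effects that had just been declared to exist. With interaction, the two numbers differ in truth. If Table 3 then showed interaction-model coefficients beside main effects in Table 2, a change of estimand could be taken for an effect of covariate adjustment.

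**Working it through.** **Inputs.** SD 18 mmHg, ICC 0.02, 48 facilities of 20 with 20% loss (SAP 2.5); 16 evaluable per facility (Protocol V1.4, section 10); 1:1:1:1 allocation (SAP 2.4), hence 12 facilities per cell. Tests: "All applicable statistical tests will be 2-sided and will be performed using a 5% significance level" (SAP 3.1). Effects: "a net reduction in mean SBP of at least 3.0 mm Hg between groups with either or both interventions compared to control" (SAP 2.5), and "the SSSC intervention strategy can reduce the systolic blood pressure of the elderly by 4.0mmHg" (Protocol section 10).

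**The plan's own figure.** SAP 2.5: "The study was designed to provide at least 80% power". Protocol section 10 adds 96.6% at 4.0 mmHg. With 24 v 24 facilities of 16, the SE is 1.481 and power is Φ(3/1.481 - 1.96) = 52.6% at 3.0 mmHg and Φ(4/1.481 - 1.96) = 77.1% at 4.0 mmHg. The stated figures return only with 48 facilities in each arm (80.9% and 96.6%, t on 94 df). That is a separate matter. Nothing below depends on it.

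**Step 1: what the coefficients are.** At given baseline SBP and time, the four cell means relative to β0 are:
- control: 0
- SS only: β1
- SSSC only: β2
- both: β1 + β2 + β3

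So:
- β1 = SS only - control; β2 = SSSC only - control
- β1 + β3 = both - SSSC only; β2 + β3 = both - SS only
- main effect of SS = ½[β1 + (β1 + β3)] = β1 + β3/2; likewise β2 + β3/2 for SSSC

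β1 equals the main effect only if β3 = 0. The SAP gives no centring and no β1 + β3/2 contrast.

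**Step 2: precision.** Variance of a facility mean = 18² × (1 + 15 × 0.02)/16 = 324 × 1.3/16 = 26.325.
- Main effect, 24 v 24: √(26.325 × 2/24) = 1.48 mmHg
- β1 or β2 under 0/1 coding, 12 v 12: √(26.325 × 2/12) = 2.09 mmHg
- β3: √(26.325 × 4/12) = 2.96 mmHg under either coding

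The ratio 2.09/1.48 is √2, whatever the SD or ICC, for balanced cells with the same residual variance. The separate SS model omits SSSC, so an SSSC effect of 4.0 mmHg would add (4/2)² = 4 to its between-facility variance. Its SE becomes √(30.325 × 2/24) = 1.59 and the ratio about 1.3.

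**Step 3: value under interaction.** Take SS alone at -3 mmHg.
- β3 = 0: β1 = -3.0, main effect = -3.0
- β3 = +1.5: β1 = -3.0, main effect = -3 + 0.75 = -2.25
- β3 = +3: β1 = -3.0, main effect = -3 + 1.5 = -1.5

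**The case against.** The strongest reply is that no primary inference depends on this. Each intervention is tested in its own single-indicator model. The interaction model is conditional on both effects existing and is there to test β3, which is the same under either coding. This stands, and it limits the point to labelling and reporting.

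A second reply is that the SAP prints the equation, defines the indicators as 0/1 and ties β0 to the control group, so the meaning can be worked out. That is true, but it does not settle which estimate fills a single Table 2 cell.

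Third, the simple effects belong in the plan. Protocol section 2.1 sets out to compare each intervention on its own, and the two together, with control. This stands too. It argues for showing these contrasts under their proper names, and against recoding that would remove them from the printed coefficients.

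Fourth, a reader might infer that Table 3 switches to simple effects, or that hyperkalemia has exactly the same fault. The documents do not go that far. SAP 5.1.2.1 does not say that the conditional model replaces the adjusted single-indicator model. SAP 5.3.2.1 separates the effect models from the interaction model and does not expressly send the latter's β1 and β2 to a table. In both places the ambiguity is possible, and it is weaker for hyperkalemia.

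**Conclusion.** The point holds as a reporting and estimand defect. If the interaction model is fitted and SAP 5.1.1 is followed as written, two different quantities go to one Table 2 cell under one label. The second has an SE up to about √2 larger (2.09 v 1.48 mmHg) and differs from the main effect by half the interaction.

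The SEs assume a single visit, equal facilities of 16 and no baseline adjustment. The planned repeated-measures model with baseline SBP would change them. The algebra does not depend on these assumptions.

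A reader might infer that the trial loses power, because at 3.0 mmHg the 0/1 β1 has 29.9% against 52.6% for the main effect (48.0% v 77.1% at 4.0 mmHg, no interaction, normal approximation). The documents do not support that reading: the separate models carry the primary tests, so these figures describe no test on which the trial relies.

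**What to change.** In SAP 5.1.1 and Tables 2 and 3:
- State that the SS and SSSC columns come from the separate, main-effect models throughout.
- State that only β3 and its p value are taken from the interaction model for the interaction column. The shell has room for the p value alone, so add a place for the estimate and interval.
- Relabel β1 and β2 as SS only v control and SSSC only v control.
- Report β1, β1 + β3, β2 and β2 + β3 in separate rows labelled as without or with the other intervention. These rows also supply the Protocol section 9 comparisons of the combination with each single intervention.

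Use the same labels in 5.1.2.1 and 5.3.2.1.

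Recoding the indicators to -0.5/+0.5 is optional. It leaves β3 and its p value unchanged, but it takes the single-intervention contrasts out of the printed coefficients. With unequal cells or on the logit scale it also need not reproduce the separate models' estimates.

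The cost is SAP wording, a contrast statement for the two sums and a few table rows. No new data and no change to the primary test are needed.

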### 5.1.2 Secondary analysis

Various secondary analysis will be conducted to examine the robustness of the conclusions of primary analysis.

#### 5.1.2.1 Controlling for potential confounders

We will test if there is any imbalance between groups in baseline variables. We will additionally include the covariates that differs significantly at the baseline ( $p<0.05$ ) to adjust confounding.

The models would be:

$$y_{ijt} = \beta_0 + \mu_{1i} + \mu_{2j} + \beta_1 x_{ij} + \beta_2 c_{ij} + \sum BZ_{ij} + \beta_3 t + e_{ijt}$$

$$e_{ijt} \sim N(0, \sigma_e^2)$$

$$\mu_{1i} \sim N(0, \sigma_{\mu 1}^2)$$

$$\mu_{2j} \sim N(0, \sigma_{\mu 2}^2)$$

Where  $i$  represents the  $i^{\text{th}}$  subjects,  $j$  represents the  $j^{\text{th}}$  cluster (facility),  $t$  represents time point  $t$ ,  $y_{ijt}$  is the SBP measured for subject  $i$  in cluster  $j$  at time  $t$  (follow-up month), baseline SBP will not be included in  $y_{ijt}$ ;  $\beta_0$  is the mean outcome in the control group at baseline;  $\mu_{1i}$  is an individual random effect to allow for multiple repeats per person;  $\mu_{2j}$  is a cluster random effect on individual baseline SBP to allow for between-cluster heterogeneity;  $x_{ij}$ , the predictor of interest, either SS or SSSC, is an indicator of the intervention for subject  $i$  in cluster  $j$  (1 indicates receive intervention while 0 indicates not receive intervention);  $\beta_1$ , the coefficient of interest, is the effect coefficient of intervention;  $c_{ij}$  is the baseline SBP measured for subject  $i$  in cluster  $j$ ;  $Z_{ij}$  is the baseline covariate other than SBP measured for subject  $i$  in cluster  $j$ ;  $e_{ijt}$  is the random error for the measurement of subject  $i$  in cluster  $j$  at time  $t$ .

If the interaction effect in primary analysis exists, then below model will be built for adjustment of covariates:

$$y_{ijt} = \beta_0 + \mu_{1i} + \mu_{2j} + \beta_1 x_{1ij} + \beta_2 x_{2ij} + \beta_3 x_{1ij} * x_{2ij} + \beta_4 c_{ij} + \sum BZ_{ij} + \beta_5 t + e_{ijt}$$

$$e_{ijt} \sim N(0, \sigma_e^2)$$

$$\mu_{1i} \sim N(0, \sigma_{\mu 1}^2)$$

$$\mu_{2j} \sim N(0, \sigma_{\mu 2}^2)$$

Where  $i$  represents the  $i^{\text{th}}$  subjects,  $j$  represents the  $j^{\text{th}}$  cluster (facility),  $t$  represents time point  $t$ ,  $y_{ijt}$  is the SBP measured for subject  $i$  in cluster  $j$  at time  $t$  (follow-up month), baseline SBP will not be included in  $y_{ijt}$ ;  $\beta_0$  is the mean outcome in the control group at baseline;  $\mu_{1i}$  is an individual random effect to allow for multiple repeats per person;  $\mu_{2j}$  is a cluster random effect on individual baseline SBP to allow for between-cluster heterogeneity;  $x_{1ij}$ , one of the predictors of interest, is an indicator of the intervention for subject  $i$  in cluster  $j$  (1 indicates receive SS while 0 indicates not receive SS);  $\beta_1$ , the coefficient of interest, is the effect coefficient of SS;  $x_{2ij}$ , one of the predictors of interest, is an indicator of the intervention for subject  $i$  in cluster  $j$  (1 indicates receive SSSC while 0 indicates not receive SSSC);  $\beta_2$ , the coefficient of interest, is the effect coefficient of SSSC;  $\beta_3$  is the effect coefficient of SS and SSSC interaction;  $c_{ij}$  is the baseline SBP measured for subject  $i$  in cluster  $j$ ;  $Z_{ij}$  is the baseline covariate other than SBP measured for subject  $i$  in cluster  $j$ ;  $e_{ijt}$  is the random error for the measurement of subject  $i$  in cluster  $j$  at time  $t$ .

These results will be presented in **Table 3**.

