## 9. Statistical Analysis

### **Baseline Data Analysis:**

Participants will be described with respect to demographic information (age, gender, ethnic group, education, etc.), anthropometrics (weight, height, BMI, etc.), physical examination (SBP, DBP, etc.), life style and diet habits, labs (serum potassium, renal function, urinary sodium, urinary potassium, urinary microalbumin, etc.), comorbidities, medication history at baseline, both overall and separately for the intervention and control groups. Categorical data will be summarized by numbers and percentages. Continuous data will be summarized by mean, SD and range if data are normal and median, IQR and range if data are skewed. We will conduct one-way ANOVA on continuous variables and  $\chi^2$  test on categorical variables to check if the baseline characteristics balanced across randomized groups and to identify potential confounding variables.

**Effect Evaluation:** Results from ITT analysis will be reported as the primary result and the one from PP analysis will be reported as the secondary result.

Primary outcome is the change in SBP from baseline to follow-up

Secondary outcome includes change in DBP from baseline to follow-up, changes in 24-hr urinary sodium and urinary microalbumin; the risk of developing cardiovascular events

We will use multilevel mixed-effects model to control the cluster effect and confounding variables. We will compare the difference of changes in blood pressure before and after the intervention between SS and non-SS, SSSC and non-SSSC, SS + SSSC and SS only or SSSC only respectively.

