## **2.4 Randomization**

The 48 eligible senior residential facilities (clusters) were randomized through a central computerized process in a 1:1:1:1 allocation ratio to the 4 intervention groups, with stratification by four regions, (Changzhi , Xi'an, Hohhot and Yangcheng). An independent statistician carried out the randomization after the baseline characteristics had been collected for study sites and individual participants. The allocation codes are kept by the statistician, and only the local staff responsible for the implementation of interventions have been informed. The outcome assessment team is independent of the staff responsible for implementing the interventions

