### 5.2.2 Analysis for events

Frailty survival models (cox proportional hazards model with mixed effects) that account for within-cluster homogeneity will be used for the analysis of all-cause mortality, cardiovascular events (fatal and nonfatal stroke, fatal and nonfatal myocardial infarction, hospitalization or death caused by congestive heart failure). The proportional hazards assumption will be confirmed using statistics and graphs based on the Schoenfeld residuals. If more than one events took place during the study period, only the first event will be counted. Separated models will be built for each intervention, either SS alone or SSSC alone. The cluster(facility) will be regarded as the random effect. The models would be:

$$h_{ij}(t) = h_0(t)\exp(\beta_1 x_{ij} + \mu_j)$$

Where  $h_{ij}(t)$  is the hazard function for the  $i^{\text{th}}$  subject in  $j^{\text{th}}$  cluster.  $h_0(t)$  denotes the baseline hazard function. ;  $x_{ij}$ , the predictor of interest, either SS alone or SSSC alone, is an indicator of the intervention for subject  $i$  in cluster  $j$  (1 indicates receive intervention while 0 indicates not receive intervention);  $\beta_1$ , the coefficient of interest, is the effect coefficient of intervention;  $\mu_j$  denotes the random effect associated with the  $j^{\text{th}}$  cluster. An additional multivariate model will be conducted to controlling for the potential unbalanced covariates at baseline, if any.

The results for event will be presented in **Table 4** and **Table 5**.

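### Covariates for the secondary adjusted models are chosen by baseline p<0.05, and the only named tests ignore clustering and flag about 13% of variables, not 5%, at the plan's ICC

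*Supplement*

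**What the plan says.** SAP 5.1.2.1 tests for imbalance between groups in the baseline variables, and then: "We will additionally include the covariates that differs significantly at the baseline", at p<0.05. The SAP does not name the test. Protocol V1.4, section 9, does: "We will conduct one-way ANOVA on continuous variables and" a chi-square test on categorical ones, "to check if the baseline characteristics balanced across randomized groups and to identify potential confounding variables". Neither test has a term for the facility. SAP 5.9, which lists departures from the protocol, does not replace them.

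SAP 5.2.2 does something similar for clinical events: "An additional multivariate model will be conducted to controlling for the potential unbalanced covariates at baseline, if any". It gives no p threshold. SAP 5.2.1 applies the primary-outcome models to the continuous secondary outcomes and reports them in Tables 2 and 3. The shells of Tables 3 and 5 leave the adjustment list blank, and Table 1 has a single p-value column across the four groups.

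Facilities were the randomised units, stratified by region, "in a 1:1:1:1 allocation ratio to the 4 intervention groups". The primary model (SAP 5.1.1) has a set specification with baseline SBP and does not use the selection rule.

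**The concern.** Two separate faults meet here.

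The first does not depend on any ICC. After randomisation, differences between groups in baseline variables are due to chance. A p value measures how unusual such a difference is. It carries no information on whether the variable predicts SBP, and that is what decides whether adjustment helps. Region shows the problem: stratification tends to balance it, so the rule will tend not to select it, although a stratification factor is a natural covariate.

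The second is that the named tests treat residents as independent when whole facilities were allocated. Their true rejection rate exceeds the nominal 5%.

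These models are meant to show that the primary conclusions are robust. A covariate list that is unknown until the baseline tests have been run is a weak check, because a reader cannot separate planned adjustment from chance selection.

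**Working it through.** The documents state no error rate for the baseline tests, so there is no figure of theirs to reproduce. The rate can be derived from their inputs.

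**Inputs**
- 48 facilities in four equal groups: 12 per group, or 24 v 24 for each factorial margin (SAP 2.4).
- 20 residents per facility: "resulting in a sample size of 960 individuals drawn from 48 clusters, each with 20 participants" (SAP 2.5).
- "an intra-cluster correlation coefficient of 0.02" (SAP 2.5). This is the only ICC in the documents. It is for SBP, and its use for other variables is an assumption.
- Level: "All applicable statistical tests will be 2-sided and will be performed using a 5% significance level" (SAP 3.1).

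**Formula.** For a variable balanced in expectation, the individual-level between-group statistic is inflated by the design effect DE = 1 + (m − 1) × ICC. The rate at which it is flagged is then
- four groups: P(χ² on 3 df > 7.815 / DE)
- two groups: 2 × [1 − Φ(1.96 / √DE)]

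**At the plan's ICC.** DE = 1 + 19 × 0.02 = 1.38.
- Four groups: 7.815 / 1.38 = 5.66, giving 12.9% (simulated 12.7%).
- Two groups: 1.96 / √1.38 = 1.67, giving 9.5% (simulated 9.1%).

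**At assumed ICCs** (not in the documents)

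| ICC | DE | Four groups | Simulated | Two groups |
|---|---|---|---|---|
| 0.05 | 1.95 | 26.1% | 26.4% | 16.0% |
| 0.10 | 2.90 | 44.1% | 44.3% | 25.0% |

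**Settings that lower the four-group rate** (ICC 0.02, then ICC 0.10)
- Half of the ICC lying between regions, which stratification balances (the half is assumed): 8.7%, 25.1% (simulated).
- Binary covariate with 30% prevalence and the ICC on the latent scale: 9.2%, 29.2% (simulated with an F test on the 0/1 variable, which is close to chi-square).
- 16 residents per facility: 11.1%, 37.3%.

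**Check of the cause.** An F test on the 48 facility means (3 and 44 df) gives 5.0% to 5.2% for ICC 0 to 0.10 when none of the ICC is regional. The excess therefore comes from ignoring the facility. This would cure the second fault only: a test at a true 5% would still choose covariates by chance.

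**The case against.** **Only secondary analyses are affected.** This stands. The primary SBP model and the main event model carry no selected covariates, and the adjusted safety analyses use a named list of conditions (SAP 5.3.2.1). Baseline SBP is in every adjusted SBP model, so some planned precision is kept.

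**The SAP names no test.** This also stands. SAP 4.2 repeats most of the protocol's baseline paragraph without the sentence on ANOVA and chi-square. That the tests ignore clustering is read from the protocol. It is a fair reading, because nothing replaces them, but it is an inference. Likewise, SAP 5.2.2 refers to unbalanced covariates without a cut-off, so one cannot say that the p<0.05 rule itself governs Table 5.

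**The flagged imbalances are real.** They do exist in the sample, and randomising facilities makes chance imbalance larger. Wanting to adjust is reasonable. The fault lies in using the p value to choose.

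**Stronger readings to avoid.** A reader might infer that 44% of balanced variables will be flagged. That needs an ICC of 0.10 for the variable and no regional share, and the documents support neither. A reader might also multiply a continuous-variable rate by all 29 individual-level items in Table 1. Baseline SBP is already in the model and region is stratified, which leaves 27, of which 11 are categorical. With the plan's ICC applied to every item, the illustration is 16 × 0.129 + 11 × 0.092 ≈ 3.1 flags, against 27 × 0.05 ≈ 1.4. Larger counts rest on ICCs that are not given.

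**Conclusion.** The point holds for the secondary adjusted models. Selection by baseline p<0.05 lets chance decide the covariates in Table 3, whatever the ICC. SAP 5.2.2 leaves the covariates for Table 5 equally open.

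In addition, the only tests named run above their nominal level: about 13% for a four-group ANOVA and about 9-10% for a two-group margin. These figures assume 20 residents per facility, the SBP ICC of 0.02 carried over to other continuous variables, and no between-facility variation explained by region. The higher figures are conditional on assumed ICCs, and they fall for binary covariates or where region explains part of the clustering.

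The documents give no ground for saying that the primary result is compromised.

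**What to change.** In SAP 5.1.2.1, replace the p<0.05 rule with a fixed list used whatever the observed imbalance. An example from data already collected is baseline SBP, region, the other factor (SSSC in the SS model, and the reverse), age, sex, BMI and baseline antihypertensive use. Use it for the adjusted SBP and DBP models, with baseline DBP for DBP. Write the list into the footnote of Table 3. The same list can define the unspecified covariates in the second sensitivity analysis of SAP 5.7.

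For the event models in SAP 5.2.2, also fix the list in advance, but keep it shorter if events are few. The example list adds nine parameters (three for region and one each for the other six), and the documents give no expected event count to show that this is affordable.

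State that baseline significance tests are not used to select covariates. Whether Table 1 keeps its p-value column is then a reporting choice that changes no estimate.

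The SAP already works this way elsewhere: SAP 5.3.2.1 names its adjustment conditions, and SAP 3.4 names the variables used to impute 24-month SBP. The change is wording only, needs no new data, and costs a few degrees of freedom.
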